#### Imaging

##### Imaging

*Ultrasound* (Hitachi Aloka Arietta 850 machine, with 18–5 Hz linear echo probe, in B mode 25 fps, in Doppler 19 fps, Tokyo, Japan) of the patellar tendon will be performed by an experienced musculoskeletal radiologist, or under the supervision of an experienced musculoskeletal radiologist. The participant will be examined in the supine position with the knees flexed for determining the structure and extended for determining vascularization. The ultrasound scan includes an assessment of patellar morphology and echogenicity and Power Doppler assessment (PDU) of the vascularity of the tendon. All mentioned aspects can be measured by performing one ultrasound per knee.

*Ultrasound tissue characterization (UTC)* of the patellar tendon will be used to determine 3D tendon integrity. Structure of the patellar tendon will be quantified using UTC. A standardized protocol will be used to take the UTC scans [36]. Participants will sit down on a treatment bench with the bench as much as possible in the popliteal fossa with approximately 90° knee flexion. An ultrasound probe (SmartProbe 12L5-V, Terason 2000 + ; Teratech) will be affixed to a tracking device (UTC Tracker, UTC Imaging) to standardize transducer tilt angle. The tracker device will move the probe automatically over the length of the tendon, capturing transverse images every 0.2 mm. The ultrasound probe in the tracking device will be placed perpendicular to the long axis of the tendon, moving from proximal to distal. Both patellar tendons will be scanned for each participant. All scans will be taken by a single examiner who is experienced with UTC. The consecutive transversal images will be used to create 3D reconstructions. The consistency of intensity and distribution of gray images will be calculated over a distance of 4.8 mm using UTC algorithms. Four echo types can be discriminated based on consistency, with echo type I representing the most stable pattern and echo type IV the least stable. Tendon structure will be quantified by calculating the percentages of these four echo types in multiple regions of interest (ROI) placed around the border of the tendon in the transverse view. ROIs will be selected at intervals no greater than 5 mm from the apex of the patella to 20 mm distally. Contours will be drawn every 5 mm and window size 17 will be used for imaging analysis. All tendons contours will be marked by trained personnel, due to practical implications. The inter- and intra-rater reliability of the processing of the scans is found to be excellent [37, 38].

##### Tendon stiffness

Patellar tendon stiffness will be assessed using myotonometric measurements with the MyotonPRO device (Myoton Ltd, Tallinn, Estonia). The measuring method of this device is based on the free oscillation technique. The following steps occur during a single measurement: (1) the device is placed perpendicular to the skin and a constant pre-pressure is applied for compressing the subcutaneous tissue; (2) a brief mechanical impulse is applied causing damped oscillation of the tissue; and (3) the co-oscillation generated in the tissue is recorded by an accelerometer. The myotonometer has good to excellent test–retest reliability and has been established in previous literature [39].

The anatomical landmark for the patellar tendon stiffness assessment will be the most painful spot in the patellar tendon but also 1 cm below the inferior pole of the patella and the midpoint of the patellar tendon. The participants will lie down on a treatment bench with their knees flexed to 90°, measured with a goniometer. In addition to stiffness measurements on the tendon, the stiffness of the rectus femoris muscle will be measured as well, at 1/3 and 2/3 of the muscle, with extended hip and knee. The myotonometric evaluation will be repeated 3 times per location. Only measures that have a coefficient of variation lower than 3% will be considered; otherwise, the measurement will be repeated.

For all imaging techniques and tendon stiffness measurements, the contralateral patellar tendon will also be examined for comparison. Here as well, if both sides are affected, the most affected side will be registered as the affected side.

##### Nutrition

A 3-Day Food Record (3DFR) will be recorded at the start and at the end of the intervention period by the use of the validated TRAQQ app of Wageningen University [40, 41]. Using this app, participants report what they have eaten for 3 days, after which the app automatically calculates the macro- and micronutrient intake. These 3 days will take place on two workdays and one weekend day. This will be measured to investigate their current nutritional status and potential causes or relationships between nutrition and the current tendon problems. Nutrients that will be measured are among others: protein and amino acid intake, total energy intake, alcohol consumption, and vitamin C intake. These nutrients were found to affect tendon health in a recent systematic review [42]. Amino acid intake is a more specific item that can be included by the use of the amino acid table that is part of the TRAQQ app and the Wageningen University. Here, the amino acid content of products is added to the Dutch food composition database. During the entire intervention period, participants will be asked not to radically change their diet. For example, changing to a vegan diet is not allowed during the study if this was not the participant’s habitual diet before the start of this study.

##### Questionnaires

Multiple questionnaires will be given at baseline, at 12 weeks, and at 24 weeks. These questionnaires involve general health and well-being (ED-5Q), central sensitization of pain (CSI), the influence of the participants’ injury on sports participation (OSTRC), categorizing subgroups within patients with PT (MSK), and a sports activity rating scale (SARS). In addition, a follow-up questionnaire will be given investigating subjective participant satisfaction with the PTLE program, the return to sports, the pain during activities of daily living, during sports and during the PTLE program, and investigating the use of co-interventions, training load, and the compliance to the supplement intake and PTLE program.

#### Other outcomes

##### Weekly logbooks

Data on compliance to the training program, mean pain score during the exercises, and sport-specific training load will be registered on a weekly basis. The questionnaire will be automatically sent weekly as a reminder. In this online questionnaire, we ask the number of training days that week and the number of matches that week. We ask which percentage of the prescribed repetitions the participant had accomplished and the precise amount of load and number of series and repetitions of the exercise program executed. The training load that will be obtained from this questionnaire is defined as the total duration of training and matches played per week (minutes) multiplied by the experienced intensity of training sessions and games using the modified Borg CR-10 Rate of Perceived Exertion (RPE) scale [43]. In addition, we ask the level of pain when performing the exercises, and we ask for reasons why the participant has not performed the prescribed exercises. Answering options are (1) lack of time, (2) pain, (3) preferring sports activities, (4) rest day, and (5) lack of motivation. We ask whether the participant has returned to their sports level or not; answering options are (1) not active in sports, (2) no return to sports, (3) returning to sport but not in desired sport, (4) returning to desired sport but not at the preinjury level, and (5) returning to preinjury level in the desired sport. We ask how satisfied the participant is with the exercise program; answering options are (1) excellent, (2) good, (3) moderate, and (4) poor.

At the end of the study, participants will be asked whether they knew which of the two supplements they received during the intervention period. The results of the weekly questionnaire are stored using a secure data collection site where data can be accessed, submitted, and modified.

### Participant timeline {13}

Participants will be recruited from April 2023 until May 2025. Upon registration and signing informed consent, the executive researcher will screen participants for potential eligibility. To prevent participants from making an unnecessary visit to the hospital, the PI will ask among others the age, absence of known inflammatory diseases or hypercholesterolemia, previous knee conditions and treatments, use of medication, and participation in other treatment programs. To increase the likelihood of the diagnosis of patellar tendinopathy, we will use a self-administered pain map, where one of the six images shows the situation of PT. The potential participant will finally complete an online VISA-P questionnaire, which should be below 80 points to be eligible for the study. If these criteria are met, the participant is invited for inclusion measurements at the hospital Gelderse Vallei.

When the participant arrives at the hospital, further screening for inclusion criteria follows. A clinical examination will be performed by an experienced sports physician. The diagnosis will be based on clinical examination: focal pain at the inferior patellar pole or patellar tendon on palpation and a single-leg-decline squat. If the potential participant meets all the inclusion criteria, he/she is allocated to either intervention or placebo and invited for another appointment at the hospital for the baseline measurements. In addition, the 3DFR will be scheduled. This will be explained, which the participant fills in at home, using the app “TRAQQ” of Wageningen University.

At baseline, a test day will take place at hospital Gelderse Vallei, containing the outcome measures stated above (blood measurements, body composition measurements, questionnaires, imaging, stiffness measurements, and functional tests; see Fig. 1B and Table 1). At follow-up (12 and 24 weeks), the clinical, radiological, and blood parameters will be repeated. The measurements will be performed in an identical way as during the baseline measurements, with the exception of the ultrasound, which is only performed at baseline and at 24 weeks (see Fig. 1B). In addition, the 3DFR will be obtained at baseline and after 24 weeks, with no nutritional assessment at 12 weeks.

**Table 1 Tab1:** Schematic diagram of the JUMPFOOD study

		V1		V2–V4			
	At home by mail or telephone	At the hospital Sports Valley	Start of study	At the hospital Sports Valley Week 0, week 12, and week 24	Online Week 6, week 18, and week 52	During the entire 24 weeks, daily	During the entire 24 weeks, weekly
Handover study information and informed consent	X						
Telephone call: discuss questions about participation	X						
Signing informed consent	X						
Online screening	X						
VISA-P	X						
Pain map	X						
Inclusion questions	X						
Hospital screening		X					
Physical examination		X					
Ultrasound		X					
Functional tests		X					
Explanation PTLE program		X					
Randomization			X				
Study measurements				X			
Body composition^b^				X			
Questionnaires^c^				X	X^a^		
Blood sampling				X			
Functional tests^d^				X			
Imaging^e^				X			
Myoton				X			
Compliance (sachets check)				X			
Supplement use						X	
PTLE program (3 times/week)^f^							X
Compliance							X

^a^Only the VISA-P is asked digitally in weeks 6, 18, and 52

^b^Consisting of length and body weight measurements and sevenfold sum of skinfolds measurements

^c^Consisting of the VISA-P, EQ-5D, MSK, CSI, SARS, OSTRC, and follow-up questions investigating satisfaction, return to sports, pain during activities of daily living, during sports and during the PTLE program, the use of co-interventions, compliance to exercise program and supplement intake, and investigating training load

^d^Consisting of the single leg decline squat and measurements of the isometric strength of the quadriceps, hamstrings, and abductors; muscle length; drop jump test; weight-bearing dorsiflexion lunge test; hoptests; and the squat vs countermovement jump

^e^Consisting of an ultrasound (grayscale and power Doppler) and UTC, with the ultrasound executed at 0 and 24 weeks and not at 12 weeks

^f^Part of usual care

Tendinopathy-related symptoms will be recorded at baseline and 6, 12, 18, 24, and 52 weeks’ follow-up (Fig. 1A) using the VISA-P score. At 6, 18, and 52 weeks, this outcome measurement will be determined using a web-based form. The follow-up questionnaire that is given at baseline and 12 and 24 weeks is also given at 52 weeks of follow-up.

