### Trial design {8}

The JUMPFOOD study is a double-blinded, 2-armed randomized-controlled superiority trial (RCT). The duration of the intervention is 24 weeks after inclusion, with an additional follow-up questionnaire at 52 weeks (see Fig. 1A, B). Test days will take place at weeks 0, 12, and 24, with the first test day marking the start of the intervention period. Randomization will be performed as block randomization with a 1:1 allocation. The JUMPFOOD study will take place from February 2023 and is expected to finish at the end of 2025.

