The primary study parameter will be the difference between intervention and placebo in the change in VISA-P score (0–100) over time. The primary outcome will first be analyzed with a linear mixed model. When the residuals of the model are not normally distributed, we will use a generalized linear mixed model instead. As independent variables, the treatment (supplement or placebo), time (time points of the measured variable) and time × treatment will be fixed factors, and the participant will be used as a random factor. Adjustments will be made for those baseline variables that are associated with the primary outcome (*p* < 0.10), using a multivariable analysis and a stepwise backward elimination strategy. Examples of potentially associated variables are baseline vitamin C and collagen amino acid intake, baseline P1NP concentrations, compliance to PTLE program, compliance to supplement use, and use of co-medication. Secondary study parameters will be reported quantitatively as well, in the most commonly used way. For the secondary study parameters, we will choose between the generalized linear mixed model and the linear mixed model in the same manner as for the primary outcome. Here, as independent variables, the treatment (supplement or placebo), time (time points of the measured variable), and time × treatment will be fixed factors, and the participant will be used as a random factor. The dependent variable is the secondary study parameter in question (with as important dependent variables/outcome measures: pain during a single leg decline squat, ultrasound imaging abnormalities, UTC findings, and tendon and muscle stiffness). The same stepwise backward elimination strategy will be used as mentioned above. For parameters that are categorical (dichotomous, nominal, or ordinal) a generalized linear mixed model will be used that is applicable for that specific secondary variable (for example a logistic mixed model for dichotomous parameters, and an ordinal mixed model for ordinal parameters). For these parameters, a similar strategy will be applied as described above.

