### Methods in analysis to handle protocol non-adherence and any statistical methods to handle missing data {20c}

Consistent with the CONSORT statement, an intention-to-treat analysis will be performed. In order to ensure the integrity of the randomization process and to offer an authentic assessment of the treatment outcomes, we will implement the intention-to-treat principle, analyzing the entire study population irrespective of their adherence to the treatment. We will carry out sensitivity analyses to assess the influence of missing values in the outcome parameter on the results. Then, we will decide on a strategy on how to handle the missing data if necessary. If data is missing “completely at random” (MCAR), we will perform multiple imputation to model the missing data within the intention-to-treat analysis, thus preserving the variability inherent in the outcome variables [44–46].

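### Participants are allocated after screening but before the separate week-0 visit, an avoidable risk of randomised participants who never start, prove ineligible or lack week-0 data

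*Protocol article*

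**What the plan says.** Participant timeline {13} describes an online screening, a hospital screening, allocation, and then a further visit. The online step ends with the primary outcome instrument: "The potential participant will finally complete an online VISA-P questionnaire, which should be below 80 points to be eligible for the study". A person who then passes the clinical examination "he/she is allocated to either intervention or placebo and invited for another appointment at the hospital for the baseline measurements". The later visit is the week-0 test day: "At baseline, a test day will take place at hospital Gelderse Vallei, containing the outcome measures stated above". Table 1 gives the same order, with randomisation in its own column between the screening visit and the week-0 visit.

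Trial design {8} describes the test days "with the first test day marking the start of the intervention period". Blood sampling, under Outcomes {12}, has the supplement taken on each test day between two blood draws, so the first intake described is at week 0.

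Table 1 puts "Explanation PTLE program" at the screening visit. The PTLE text under Intervention description {11a} puts the first instructions at the start of the intervention period.

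On analysis, section {20a} says "The primary outcome will first be analyzed with a linear mixed model", with time, treatment and their interaction as fixed factors and participant as a random factor. Adjustment for associated baseline variables follows, with P1NP and nutrient intake among the examples. Section {20c} commits to intention-to-treat, "analyzing the entire study population irrespective of their adherence to the treatment".

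**The concern.** The article describes nothing between the screening visit and the week-0 visit that requires the allocation to exist already. The gap leaves room for three different events after randomisation:

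- **Not starting.** A participant may not return and so never take the supplement.
- **Proving ineligible.** Eligibility criteria {10} excludes athletes who gave blood in the two months before each test day. For week 0 this can be confirmed only on that day.
- **Missing week-0 measurements.** A non-attender lacks the week-0 VISA-P, P1NP, UTC, stiffness and questionnaire data, and possibly the diet record that is arranged around the same appointment.

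Each such person uses one of 76 randomised places in a trial with little reserve. Section {20c} discusses missing values of the outcome but not of baseline covariates, so a participant without week-0 P1NP or diet data may leave any adjusted model that keeps those terms.

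**Working it through.** **1. Order of events**

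| Step | Where stated |
|---|---|
| Online VISA-P, pain map, inclusion questions | {13}, Table 1 |
| Hospital screening, with examination, ultrasound, functional tests | {13}, Table 1 |
| Allocation | {13}, Table 1 |
| Week-0 visit: VISA-P, blood including P1NP, imaging, stiffness, questionnaires | {13}, Table 1, Fig. 1 |
| First supplement intake, between the two week-0 blood draws | {12}, Blood sampling |

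Allocation precedes the first intake by one visit. The documents give neither the length of this gap nor the proportion who fail to return.

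**2. The plan's own sample size**

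Inputs from Sample size {14}: difference 13, SD 19, power 80%, significance level 0.05, loss 9%.

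- Standardised effect: 13/19 = 0.684.
- A two-sided two-sample t-test needs 34.5, so 35 per arm and 70 in total. This matches the plan. Sidedness is not stated; a one-sided test would need 28 per arm (56 in total), which does not match.
- Allowance for loss: 70/0.91 = 76.9, against the stated 76. Conversely, 76 × 0.91 = 69.2, so the reserve is fully used before any further loss.

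**3. Effect of a further loss before week 0**

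The rate p is an assumption, because the documents give none. If it comes on top of the 9%, the number left is N = 76 × (1 − p) × 0.91. Power is from the same t-test with N rounded down to whole participants.

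| Assumed p | Lost before week 0 (76p) | N | Whole participants | Power |
|---|---|---|---|---|
| 0% | 0 | 69.2 | 69 (35 + 34) | 80.0% |
| 3% | 2.3 | 67.1 | 67 (34 + 33) | 78.8% |
| 5% | 3.8 | 65.7 | 65 (33 + 32) | 77.5% |
| 8% | 6.1 | 63.6 | 63 (32 + 31) | 76.2% |

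Without rounding N down, the last three powers are 78.8%, 78.0% and 76.6%. If the 9% is meant to include people lost before week 0, the first row applies and nothing changes. The table counts each such person as contributing nothing to the comparison, which is the least favourable case.

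**4. What the analysis can still use**

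- *Outcome.* A mixed model fitted by likelihood keeps any participant with at least one VISA-P value at a modelled time point; a complete record is not needed. Of the follow-up scores, "At 6, 18, and 52 weeks, this outcome measurement will be determined using a web-based form", so a person who missed week 0 can still supply data.
- *Change.* The text does not say that the screening VISA-P may stand in for the week-0 value. Without a starting value, or with no later value, a participant says little about change.
- *Covariates.* A mixed model does not fill in a missing covariate. If P1NP or nutrient intake survives the backward elimination, participants without it are dropped from that model unless it is imputed.

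**5. Timing of the exercise explanation**

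Table 1 places it at the screening visit. Section {11a} places the first instructions at the start of the intervention period, which section {8} equates with the first test day. Section {8} does not itself mention the explanation, so the conflict is between Table 1 and {11a} read with {8}.

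**The case against.** A reader might infer that these participants are randomised with no baseline data and that the promised intention-to-treat analysis cannot include them. The documents do not support that. An online VISA-P is required before allocation, and Table 1 lists ultrasound and functional tests at the screening visit. The mixed model accepts partial records, three later VISA-P scores need no visit, and section {20c} commits to the whole population and provides for sensitivity analyses and, under a stated condition, multiple imputation. A missed week-0 visit is missing data, not a bar to inclusion. This part of the objection stands in full.

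A reader might also suspect selective loss between the arms. Supplement numbers cannot be traced to a treatment, and participants, care providers, assessors and analysts are blinded ({16b}, {16c}, {17a}), so loss before the first intake has little means of depending on the arm. Such losses leave slightly unequal analysed numbers but do not undo the block randomisation. This stands too.

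The three kinds of participant must also be kept apart. Someone who begins exercising early or proves ineligible can still be measured at week 0; only a non-attender lacks those data.

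Finally, the loss rate is assumed, and the article does not describe supplement logistics, so a practical reason for early allocation cannot be ruled out. That limits the size of the point. It does not answer why allocation should precede the last eligibility check and the baseline measurements when the product is first taken afterwards.

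**Conclusion.** The point holds as an avoidable design weakness of modest size. Allocation before the week-0 visit allows randomised participants who never start, prove ineligible or lack week-0 measurements. The documents do not say how they would be handled in the covariate-adjusted model, or whether the screening VISA-P may replace the week-0 value. Intention-to-treat remains possible, and no bias between the arms is shown.

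The cost in power runs from nothing, if the 9% already covers these losses, to about four percentage points (80% to about 76%) if a further 8% is lost. This rests on the assumed 3–8% range and on the plan's own difference of 13 and SD of 19. The inconsistent timing of the exercise explanation is a separate, minor matter that applies to both arms alike.

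**What to change.** For participants not yet enrolled, change Participant timeline {13} and Table 1 so that the participant number is assigned on the week-0 test day. Do this after eligibility is reconfirmed, including recent blood donation, and after the baseline VISA-P and fasting sample are taken, immediately before the first supplement intake. This settles the blood-donation criterion for week 0 only; donations before the week-12 and week-24 visits cannot be known at entry under any order.

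For participants already allocated, state whether the screening VISA-P may serve as the starting value when week 0 is missing, that they stay in the intention-to-treat set, and how missing baseline covariates are treated.

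Separately, reconcile the timing of the exercise explanation in Table 1 with sections {11a} and {8}.

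The cost is small: an amendment to the wording, numbered supplements on site on the test day (already needed for the post-intake blood sample), and a slot for allocation in the test-day schedule.
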